# A study protocol for an mHealth, multi-centre randomized control trial to promote use of postpartum contraception amongst rural women in Punjab, Pakistan

**DOI:** 10.1186/s12884-019-2427-z

**Published:** 2019-08-08

**Keywords:** Behaviour change, Family planning, Phone-based intervention, Antenatal care, Postnatal care, Non-inferiority

## Abstract

**Background:**

Provision of family planning services during the immediate post-partum phase is considered effective and cost-efficient for promoting healthy timing and spacing of pregnancies. This research aims to test the effectiveness of mobile phone-based interventions in promoting use of postpartum contraception. Moreover, it will also test the non-inferiority of text and voice messages compared to interactive phone-based counselling.

**Methods:**

A three-arm, 10-month, multicentre, randomized controlled trial will be conducted at 15 social franchise (SF) health facilities in Punjab province of Pakistan. Pregnant women aged 15–44 years who are in their first or second trimester and have a mobile phone for their own use will be eligible to participate in this study. The participants will be randomly allocated to one of three study arms: a) voice and text messages; b) interactive telephone-based counselling; or c) control arm (no additional phone-based support). The intervention counselling module will be developed based on the Integrated Behaviour Model which was recently adapted, and tested for the family planning context in Pakistan. It will broadly cover birth-preparedness, importance of birth spacing, and postnatal care. The phone-based intervention aims to improve women’s ability to use contraception by providing them with information about a range of methods, access to family planning methods through outlets such as Suraj SF providers, connecting them with MSS field health educators to help them reach the centres, motivation by re-enforcing the benefits of contraceptive use on women’s quality of life, and dispelling myths and misconceptions about modern contraceptive methods. Risk differences will be used as the measure of effect of the intervention on the outcomes.

**Discussion:**

The study findings will highlight effectiveness of mobile phone in raising awareness of maternal health and contraception, which in turn, is expected to be translated into increased proportion of: at least four antenatal visits, skilled birth or institutional delivery, postpartum contraceptive use, postnatal check-up, child immunization, and breastfeeding. Moreover, if the text and voice messages approach is proven to be non-inferior to interactive calls, it will provide evidence to making promotion of healthcare less resource intensive, and thereby contribute in improving the efficiency of the healthcare system.

**Trial registration:**

This trial was prospectively registered with the Clinical Trials registry (NCT03612518) on August 2nd, 2018.

**Electronic supplementary material:**

The online version of this article (10.1186/s12884-019-2427-z) contains supplementary material, which is available to authorized users.

## Background

More than 50% of the estimated 303,000 annual maternal deaths globally occur in six developing countries, including Pakistan [1]. Across the globe, efforts to decrease maternal mortality have gained momentum, particularly in light of the Sustainable Goal agenda that states by 2030 no country should have a maternal mortality ratio higher than 70 per 100,000 live births [2]. Further, poor maternal health outcomes have negative implications for newborn and child health. Family planning is a proven, cost-effective way to prevent both maternal and newborn morality [3].

To reduce the risk of adverse maternal, perinatal, and infant outcomes, the World Health Organization (WHO) recommends an interval of at least 24 months between delivery and the subsequent pregnancy (birth-to-pregnancy interval) [4]. Evidence shows that short birth intervals increase the risk of maternal, newborn, infant, and under-5 mortality [5]; and is associated with an increased risk of preterm birth, low birth weight [6], stunting, and underweight children [6].

### Pakistan context

The maternal mortality ratio in Pakistan remains high at 276 per 100,000 live births with only 26% of ever-married women using a modern family planning method despite there being universal awareness of family planning [7], of which 37% discontinue use within 12 months [7]. Reasons for method discontinuation include experiencing side effects or health concerns, unavailability of the method, and lack of access to health services [7]. The current unmet need for family planning is 20%, and it is estimated that satisfying 20% of this unmet need could reduce maternal deaths by 29% annually [7, 8].

Pakistan has one of the highest unmet needs for postpartum family planning among low- and middle-income countries [9]. Though couples’ desire for another child decreases with the birth of each child [7] an alarmingly low proportion of women, 13%, adopt a modern contraceptive method post-partum [7]. It is estimated that the desired number of children is approximately one less than the Total Fertility Rate (TFR) of 3.8 [7].

### Rationale

#### Post-partum contraceptive uptake

Multiple encounters with the health care system during the late ante-natal and immediate post-partum period - and provision of family planning (FP) services during this time are considered effective and cost-efficient methods to promote healthy timing and spacing of pregnancy [10]. To this end, several approaches have been used to interact with women and husbands during either or both antenatal and postnatal periods and through integration with other health service [11–15]. A recent study shows that quality ante-natal services substantially increase the likelihood of postpartum contraceptive uptake. Women are most receptive to advice and counselling regarding FP during the ante-natal and early post-partum period [16] [17],. However, after discharge, most women do not return to health facilities for follow-up visits, presenting a crucial missed opportunity for FP service providers [17]. Due to the high proportion of post-partum women who are lost to follow up, the potential to increase postpartum family planning (PPFP) has not been realized [17].

Although the impact of these interventions is positive, the research is still in nascent stages [9]. There is a dire need for evidence around immediate postpartum family planning services in Asia and Africa [18]. Additionally, to better understand the behavioural indicators that influence the decision to use a modern contraceptive method, there is a need to develop theory-driven interventions [19].

#### Mobile penetration

The declining prices for mobile phones and mobile services and unprecedented increase in mobile penetration [20] [21],, is expected to facilitate the use of mHealth initiatives in resource limited settings [22] [21], [23],. Previous interventions have used mHealth approaches to promote postpartum [23] and post-abortion FP use [24], however, a recent systematic review found no robust evaluations on postpartum FP use. Interventions with robust evaluation methodologies are necessary to establish efficacy of mHealth approaches for increasing postpartum family planning [25].

Mobile penetration in Pakistan is expected to increase from 75 to 95% by 2020 [7]. A recent client exit interview found that approximately two-thirds of Marie Stopes Society (MSS) Social Franchise (SF) clients own a cell phone [26]. High mobile phone ownership presents an opportunity to utilize mHealth approaches to promote postpartum adoption of modern FP methods.

To contribute to current gaps in the literature, PPFP will test whether phone-based support to women during pregnancy and after delivery improves the uptake of immediate postpartum contraception. The mobile health (mHealth) intervention consists of two groups: 1) text and voice messages and 2) interactive phone calls by skilled professionals. Further PPFP explores whether a specific mode of communication is more effective than the other. If text and voice messages are as effective as interactive calls, it presents the opportunity to decrease human resources and make PPFP less resource intensive, consequently increasing scalability and sustainability of the intervention.

### Theoretical framework

PPFP’s counselling module will be based on the *Integrated Behavior Model* which was recently adapted and validated for modern contraception uptake amongst rural women in Pakistan. This validated model (Fig. 1) shows that the relationship between *Perceived Norms regarding FP* and *Intention to adopt a modern family planning method* is mediated by a *Positive Attitude towards FP* and *Personal Agency to use contraception*. Moreover, the model postulates that women’s attitude towards family planning has two distinct dimensions: 1) myths and misconceptions surrounding modern family planning and 2) women’s belief in the positive impact of modern family planning on their lives or *Positive Attitude*. A woman’s *Positive Attitude* towards family planning is predicted by her *Myths and Misconceptions* and *Perceived Norms* related to modern contraception. Furthermore, *Personal Agency* is also predicted by her *Perceived Norms*. Subsequently, *Personal Agency* and *Positive Attitude* emerge as the two direct predictors of *Intention* to adopt family planning, while *Intention* and *Personal Agency* predict modern contraceptive uptake.

**Fig. 1 Fig1:**
[figure not shown]
Theoretical Framework

Conceptually, the intervention will aim to improve women’s *capability* to use contraception by providing information about range of methods, *opportunity* to adopt contraception by informing them about *Suraj* SF providers from where they can get services and connecting them with MSS Field Health Educator (FHE) to help them reach the facility, and *motivation* by re-enforcing the benefits of contraceptive use on women’s quality of life, dispelling myths and misconceptions, and providing support for side-effects [27].

## Methods

### Study objectives

#### Primary objective

Whether provision of information through structured automated text and voice messages are effective in increasing the use of post-partum contraception;Whether provision of information through structured interactive phone-calls are effective in increasing the use of post-partum contraception; andWhether the automated text & voices messaging approach is as effective as interactive phone-based counseling to increase use of postpartum contraception

#### Secondary objective

What are the individual and environmental factors that influence women’s intention to adopt postpartum contraception?

### Study design

PPFP is designed as a three-arm randomized controlled trial across 15 MSS’ social franchise health facilities.

### Study setting

PPFP will be a three-arm, 10-month, multi-centre, randomized controlled trial that is conducted at 15 MSS Suraj social franchise (SF) health facilities, in Punjab province of Pakistan. The target population for this study is pregnant women between 15 and 44 years old who are in their first or second trimester and have access to a mobile phone. Data collection will take place between March 2018 – March 2019 including a three-month recruitment period. FHEs will visit potential respondents at their homes to recruit them for the study. Baseline questionnaires will be administered immediately after recruitment while the endline interview will take place 60 days following childbirth.

#### MSS Suraj social franchise providers

Private providers that have been inducted into the MSS social franchise network and trained for the provision of quality FP services. In addition to these providers, each SF catchment area includes field health educators who conduct meetings and door-to-door visits within the community to promote the uptake of family planning. The MSS social franchise network is comprised of 700 franchises operating in the rural and far flung areas of Sindh, Punjab, and Khyber Pakhtunkhwa provinces, with the catchment area for each provider covering a population of 20,000-25,000.

### Eligibility criteria (inclusion/exclusion)

Married pregnant women with gestational age up to 20 weeks, between 15 and 44 years old, literate i.e. able to read and understand sample family planning messages on the phone, have regular access to a cell phone, and is a permanent resident in the catchment area will be eligible to participate in the study. Women who are not pregnant, or pregnant with gestational age beyond 20 weeks, not between 15 and 44 years of age, illiterate i.e. unable to read or understand sample family planning messages on the phone, does not have regular access to a cell phone, not a permanent resident of the catchment area, and don’t provide consent will not be eligible for the study.

### Interventions

PPFP is a behavior change intervention that aims to improve maternal and neonatal health outcomes by promoting uptake of postpartum contraception. Participants in either of the intervention arms will receive health education and health communication messages that aim to increase postpartum family planning, as well as messages on birth-preparedness and post-natal care. Participants in this study will be randomly assigned to one of three groups: group one will receive this information through text and voice messages; group two through interactive phone calls from a trained professional; while participants assigned to group 3 will not receive phone-based health education messages but can contact their FHE, Suraj provider to the MSS helpline for any information they may need.

#### Health education message development

The development of health education materials will occur in several phases:Researchers will assess the feasibility of an mHealth intervention through in-depth interviews with MSS field health educators who have been working at the selected study sites and with the target population for several years.Researchers will develop FP, birth-preparedness, and post-natal care messages using feedback from FHEs, a validated culturally congruent FP behavior change framework, WHO guidelines, and national guidelines. Further, researchers will seek expert opinions from professionals with experience designing behavior change interventions, training service providers on family planning and safe motherhood, and direct experience working in this field. All messages will be developed in English and later translated to the local language, Urdu.Researchers will pre-test all messages and voice call scripts using cognitive interviews with a subsect of the target population to gather feedback. Additionally, researchers will gather feedback from experts and use findings from both groups to further refine the health education messages.All messages will be tailored to various stages of change for family planning adoption.

Additional information for both intervention arms is included below:

#### Group I: voice and text messages

Participants in this group will receive a mix of voice messages and text messages in the local language. Each participant will receive twenty voice messages over a six-month period (120 days pre-natal and 42 days post-partum) regarding family planning, birth-preparedness and post-natal care. Initially, study participants will receive one voice message a week with the frequency increasing to two messages during the third trimester of the pregnancy and for 42 days following delivery. Postpartum voice messages will consist of a congratulatory message, counselling on maternal and neonatal health needs, breastfeeding, immunization, and planning future pregnancies. Messages will emphasize the need for birth spacing to ensure good health and wellbeing for both the mother and child. Messages will focus on Intra-uterine Contraceptive Devices (IUCDs) because of its effectiveness, high demand [7] and acceptability [28] [29], in social franchise settings.

Similarly, researchers will develop a text message library comprising of messages based on the same themes as the voice messages. Married women of reproductive age (MWRA) will start receiving text messages after the first voice message, at a frequency of two messages per week throughout the intervention period. We will receive read and delivery reports of SMS messages which we will use to build a database of the messages delivered and read by participants. In case of the intervention not yielded an impact, the read reports will be critical in isolating participants who had actually read the messages versus participants who merely received the messages.

Additionally, MWRA will be connected to their respective FHEs and respective Suraj SF providers for additional information and counseling on family planning, birth preparedness, and post-natal care.

#### Group II: interactive phone calls

Participants in this group will receive interactive phone calls from the MSS helpline call centre. These phone calls will be completed by skilled health practitioners (nurses or lady health workers) in the local language. Each participant will receive nine phone calls over a six-month period (120 days pre-natal and 42 days post-partum). Study participants will receive one call every month during the second and third trimester of the pregnancy, one call following delivery and two calls over the next 42 days. Participants will receive health education messages based on the same themes as group one but will have the additional advantage of asking questions to clear any ambiguities. As per standard practice, these calls will be recorded for quality assurance purposes. In case of the intervention not producing an impact, we will build a database by listening to the calls and determine the number of times messages were delivered appropriately for each participant. This will help us in isolating participants to whom messages were appropriately delivered.

Women reporting complications relating to pregnancy, new-born, and contraceptive method use will be referred to nearest public or private health facility.

### Modifications

Researchers will make modifications to the frequency of messages or phone calls during the intervention, if deemed necessary. Researchers will aim to retain participants for follow-up data collection in cases where they discontinue participation in the intervention.

### Adherence/monitoring

The project team will closely monitor the number of messages delivered successfully as well as the number of voice calls attended and the duration of these phone calls. It important to note that a limitation of this study is the inability to track whether the study participant read the text messages or listened to the voice messages until follow-up data collection.

### Concomitant care

The government of Pakistan has a lady health worker (LHW) program operating across the country that also aims to increase contraceptive uptake. However, as participants in the study will be randomized at the individual level, the project team does not expect the LHW program to influence the results of this study. We will capture data on interactions that the participants may have with the LHWs, and subsequently, use it as a control variable in the analysis.

### Outcomes

The following measures will serve as outcomes of interest to evaluate the effectiveness of both interventions:

#### Primary outcome of interest

Action:Proportion of subjects enrolled in each of the three groups who adopt any modern FP method to delay next pregnancy (by type contraceptive method and time within 42 days of postpartum period).Proportion of women reported to be exclusively breastfeeding the newbornProportion of women reported to immunize the newborn at birthProportion of women delivered in health facility or skilled birth professional

#### Secondary outcomes of interest

Intention: The proportion of subjects enrolled in the program who state that they intend to adopt any modern FP method to delay their next birth by 24 months (by type contraceptive method and time within 42 days of postpartum period).

Client satisfaction: Score of women’s satisfaction with postpartum family planning services.

#### Process measures

MWRA’s modern FP awareness scoreMWRA’s maternal and newborn health knowledge score of MWRAMWRA’s scores on FP behavior change scales: Perceived norms, myths and misconception, positive attitude, personal agency

### Participant timeline

The first two months will encompass the inception phase whereby implementation plan for the study will be drafted and finalized, instruments will be finalized, and database will be developed for data collection (see Fig. 2). Months three to five will span the recruitment phase for the study whereby field workers will identify pregnant women, recruit eligibility women into the study, and collect baseline data from them. Months six to twelve span the intervention phase including the final follow-up survey which will be conducted on the 60th day after birth.

**Fig. 2 Fig2:**
[figure not shown]
Participant Timeline

### Sample size

An estimated sample size was extracted for each of the research questions. First, we estimated the sample size for the second hypothesis which was based on testing non-inferiority between text/voice messages and interactive phone calls. Non-inferiority tests require relatively higher sample sizes compared to superiority trials. We calculated a sample of 840 (420 in each group) using the following assumption: a non-inferiority margin of ten percentage points (from 25 to 15%) in the use of postpartum contraception within 42 days, 80% power, 0.025 level of significance (one-sided test), 2% missing data/non-response, 8% lost-to-follow-up^1^, and 20% aggregated chance of abortion/miscarriage/fetal loss. We found that an additional sample of 130 sample would be required in the control arm to detect an increase of 15%-points (from 18% [30] to 33%) in the use of PPFP between mobile supported interventions and standard care. This was estimated by using a pre-determined sample of intervention arms (i.e. 420), 0.05 level of significance, while holding other parameters constant. PASS version 11.0 was used for sample size calculation.

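### At the 25% rate that sizes the non-inferiority test, the 10-point margin exceeds the implied 7-point benefit of calls, and the 'as effective' conclusion is not tied to beating control

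*Protocol article*

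**What the plan says.** All the relevant rates are in the Sample size section of the protocol article. The non-inferiority comparison of text/voice messages (Group I) with interactive calls (Group II) uses "a non-inferiority margin of ten percentage points (from 25 to 15%) in the use of postpartum contraception within 42 days", with "80% power, 0.025 level of significance (one-sided test". The attrition allowances are "2% missing data/non-response, 8% lost-to-follow-up^1^, and 20% aggregated chance of abortion/miscarriage/fetal loss", and the result is "We calculated a sample of 840 (420 in each group". The control arm of 130 is sized separately, "to detect an increase of 15%-points (from 18% [30] to 33%) in the use of PPFP between mobile supported interventions and standard care".

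The Primary objective section lists three questions: whether text/voice works, whether calls work, and whether "the automated text & voices messaging approach is as effective as interactive phone-based counseling". They stand side by side, and the third is not made conditional on the first. The Discussion part of the abstract attaches the practical conclusion, a less resource-intensive service, to the third question: "if the text and voice messages approach is proven to be non-inferior to interactive calls". The Statistical methods section specifies risk differences from a binomial model with identity link and 95% confidence intervals.

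**The concern.** A non-inferiority margin should be smaller than the effect that the reference treatment is assumed to have over no treatment. Otherwise an arm that does nothing can meet the criterion. Here the tolerated floor for text/voice (15%) lies below the rate assumed with no phone support (18%), so at the 25% call rate the margin preserves none of the implied benefit of calls.

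The control arm could prevent this from mattering, but no stated rule makes the 'as effective' conclusion depend on it. That conclusion would be used to justify replacing counsellors with automated messages. A related problem is that the section uses two different rates for the call arm, 25% and 33%, and whether the margin is defensible depends on which one is meant.

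**Working it through.** **Inputs (Sample size section).** Margin 10 points; call rate 25% for non-inferiority; mobile-arm rate 33% and control rate 18% for superiority; one-sided 0.025; 80% power; losses 2% + 8% + 20% = 30%; 420 per intervention arm; 130 controls.

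**1. The plan's own figures.** Evaluable n per arm = 2 × 0.25 × 0.75 × (1.960 + 0.842)² / 0.10² = 294.3. Dividing by 0.70 gives 420.5, so the stated 420 is reproduced from 25%. Evaluable numbers are 420 × 0.70 = 294 per intervention arm and 130 × 0.70 = 91 controls. With 294 against 91, 33% against 18% and two-sided 0.05, power is 81%, so 130 is reproduced too.

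**2. Margin against implied effect.**

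| Call rate | Benefit over 18% | Floor (rate - 10) | Floor against control |
|---|---|---|---|
| 25% | 7 points | 15% | below |
| 33% | 15 points | 23% | above |

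**3. Probability of declaring non-inferiority.** P = Φ((0.10 + p_text - p_call)/SE - 1.96), where SE² = [p_text(1 - p_text) + p_call(1 - p_call)]/294.

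| Calls / text | SE | (0.10 + difference)/SE | P |
|---|---|---|---|
| 25 / 25 | 0.0357 | 2.80 | 80% |
| 25 / 18 | 0.0338 | 0.89 | 14% |
| 18 / 18 | 0.0317 | 3.16 | 88% |
| 33 / 33 | 0.0388 | 2.58 | 73% |
| 33 / 18 | 0.0354 | -1.41 | 0.04% |

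At 33%, 80% power would need 2 × 0.33 × 0.67 × (1.960 + 0.842)² / 0.01, or 348 evaluable. That is 348/0.70 = 498 enrolled per arm.

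**4. Effect of also requiring text/voice to beat control.** Simulation with 294/294/91 evaluable women and two-sided 0.05 for superiority. Of each pair of joint results, the first uses a pooled z-test for text against control and the second an unpooled confidence interval, which is closer to the planned risk-difference analysis.

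| Calls / text / control | Non-inferiority alone | Non-inferiority and text > control |
|---|---|---|
| 25 / 18 / 18 | 14% | 0.8% / 1.2% |
| 18 / 18 / 18 | 88% | 2.2% / 3.6% |
| 33 / 33 / 18 | 73% | 63% / 65% |
| 25 / 25 / 18 | 80% | 24% / 30% |

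The first two rows show the protection gained, the last two the power lost. The loss is large at 25% because 91 evaluable controls give only about 27% power (pooled test) for 25% against 18%.

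**5. Shrinking the margin instead.** A 7-point margin at 25% needs 0.375 × (1.960 + 0.842)² / 0.07², or 601 evaluable. That is 601/0.70 = 859 enrolled per arm.

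**The case against.** The case on the other side has four parts.

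- **The 7 points are inferred.** They combine the 25% of one calculation with the 18% of another. The only intervention-against-control effect that the section states is 15 points, and against that a 10-point margin leaves a floor above control. This stands, and it limits the point to the 25% assumption. It does not remove it: the margin is written from 25%, and the 420 follows from 25%. The arms cannot be sized on one rate and the margin defended on the other.
- **The control arm is already there.** Text/voice against control is the first primary objective and has its own sample size. A reader might infer that the trial has no assay sensitivity. The documents do not support that, since a concurrent control supplies much of it. What the article lacks is the link: it lets the non-inferiority result carry the practical conclusion alone. A failed superiority test could also be put down to the small control arm.
- **The 88% is not an error rate of the non-inferiority test.** At 18/18 the two modes are equal, and declaring non-inferiority is correct for the hypothesis tested. Any margin behaves this way with enough power. The figure bears on the missing link to control, not on the 15% floor; the figure for the floor is 14%.
- **A decision rule may be left to the analysis plan.** That is fair for the detail of the rule. The margin and the two rates, however, are fixed in this document.

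**Conclusion.** The point holds in a limited form. On the rate that sizes the non-inferiority test, the margin (10 points) is larger than the implied benefit of calls (7 points), and a text/voice arm no better than control satisfies the hypothesis. The test would then succeed in about 14% of trials at 25/18, against the nominal 2.5% that applies at the 10-point boundary.

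A reader might go further and infer that an ineffective text/voice arm would probably be declared as effective as calls. The figures do not support that when calls work: the probability is 14% at a 25% call rate and 0.04% at 33%. It becomes likely only when calls also do little.

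The sample-size arithmetic is correct for its inputs. What needs repair is the conflict between 25% and 33%, the margin's relation to the control rate, and the missing link between the third conclusion and the first. The figures assume 30% attrition in every arm, independent observations (no allowance for clustering by facility or field health educator) and normal-approximation tests.

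**What to change.** 1. Reconcile the 25% and 33% assumptions for the call arm and restate the power. If 33% is meant, non-inferiority power with 420 enrolled per arm is 73%, and 80% needs about 498 per arm.
2. If 25% is kept, state in the Sample size section that the 10-point margin exceeds the implied 7-point benefit of calls, so non-inferiority alone shows no retained effect.
3. Allow the 'as effective' conclusion only if the lower 95% limit of Group I minus Group II is above -10 points and Group I is superior to control, both from the risk-difference intervals already planned.
4. Report the Group I against control and Group II against control differences, with confidence intervals, beside the non-inferiority result.

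These are changes of wording and need no extra participants, but they cost power, which should be disclosed. The combined claim has about 63-65% power at 33/33/18 (against 73% for non-inferiority alone) and about 24-30% at 25/25/18 (against 80%). If 25% is the working assumption, adequate power for the combined claim would need a larger control arm. Narrowing the margin to 7 points would cost far more, about 859 enrolled per intervention arm.

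### The two sample size calculations assume different contraceptive use in the same intervention arms (25% and 33%), so 80% power cannot hold for both questions

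*Protocol article*

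**What the plan says.** The Sample size section of the protocol article works in two steps.

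- **Non-inferiority, text/voice against calls.** The assumption is "a non-inferiority margin of ten percentage points (from 25 to 15%) in the use of postpartum contraception within 42 days", with "80% power, 0.025 level of significance (one-sided test"), "2% missing data/non-response, 8% lost-to-follow-up" and "20% aggregated chance of abortion/miscarriage/fetal loss". The result is 420 women per arm, 840 in all.
- **Intervention against control.** A further 130 control women are required "to detect an increase of 15%-points (from 18% [30] to 33%) in the use of PPFP between mobile supported interventions and standard care". On the remaining inputs the text says: "This was estimated by using a pre-determined sample of intervention arms (i.e. 420), 0.05 level of significance, while holding other parameters constant".

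The Primary objective section lists three questions on the same footing: text/voice against control, calls against control, and text/voice against calls. The Primary outcome section ties adoption of a modern method to the first 42 days after birth.

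**The concern.** The rate in the intervention arms is a single unknown quantity. It cannot be 25% when those arms are compared with each other and 33% when they are compared with control.

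Each choice also makes its own sample smaller. Below 50%, a lower rate means a smaller binomial variance, so 25% reduces the non-inferiority sample. A higher intervention rate means a larger gap over 18%, so 33% reduces the control arm.

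If 25% is right, the expected benefit over control is 25 − 18 = 7 points, less than half of the 15 points that sized the control arm, and a null result would be the likely outcome even if the messages work. If 33% is right, 420 per arm is too few for the stated non-inferiority power.

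The rate also changes what the margin means. A 10-point loss from 25% ends at 15%, below the assumed 18% in control. The same loss from 33% ends at 23%, above it.

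**Working it through.** **Inputs (Sample size section).** Rates 25% (non-inferiority) and 33% against 18% (superiority); margin 0.10; one-sided 0.025 and 80% power; 0.05 for superiority, taken as two-sided because one-sided does not reproduce 130; losses 2% + 8% + 20% = 30%; 420, 420 and 130 enrolled. Evaluable: 420 × 0.70 = 294 per intervention arm and 130 × 0.70 = 91 controls. The two intervention arms are taken as truly equal, which is the assumption that reproduces 420.

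**1. Reproduce 420.** n = 2p(1 − p)(1.960 + 0.842)² / 0.10². With p = 0.25: 2 × 0.25 × 0.75 × 7.849 / 0.01 = 294.3. Divided by 0.70 this is 420, as stated.

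**2. Reproduce 130.** Power = Φ[(d − 1.96·s0) / s1], where s0 is the standard error under the pooled rate and s1 the standard error under the two separate rates. For 18% against 33% with 91 and 294 women:
- pooled rate 0.2945, s0 = 0.0547, s1 = 0.0487
- (0.15 − 1.96 × 0.0547) / 0.0487 = 0.88, so power is 81.0%
- unpooled test: Φ(0.15 / 0.0487 − 1.96) = 86.8%

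The smallest control group for 80% power is 89 evaluable; 89 / 0.70 = 127, close to 130. With 420 in the intervention arm and a continuity correction it is 91, and 91 / 0.70 = 130 exactly.

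Both stated sizes therefore follow from their own inputs.

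**3. Put 33% into the non-inferiority calculation.** Standard error = √(2 × 0.33 × 0.67 / 294) = 0.0388. Power = Φ(0.10 / 0.0388 − 1.96) = Φ(0.62) = 73.2%. For 80%: 2 × 0.33 × 0.67 × 7.849 / 0.01 = 347.1, so 348 evaluable, and 348 / 0.70 = 498 enrolled per arm against 420.

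**4. Put 25% into the superiority calculation.** For 18% against 25% with 91 and 294 women:
- pooled rate 0.2335, s0 = 0.0507, s1 = 0.0475
- (0.07 − 1.96 × 0.0507) / 0.0475 = −0.62, so power is 26.8%
- unpooled test: Φ(0.07 / 0.0475 − 1.96) = 31.3%
- both intervention arms combined (91 against 588): 29.0% with the pooled-variance test, 36% unpooled

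**5. Look for a rate that serves both.**

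| Common intervention rate | Non-inferiority power | Superiority power, one arm against control (pooled variance) |
|---|---|---|
| 25% | 80.0% | 26.8% |
| 30% | 75.4% | 62.5% |
| 32% | 73.9% | 75.6% |
| 33% | 73.2% | 81.0% |

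Non-inferiority needs a common rate of at most about 25.0% to reach 80%. Superiority needs at least about 32.8%, or 31.9% with the intervention arms combined. The ranges do not meet. The best value of the smaller of the two powers is 74%, at a rate near 32%. Using the unpooled test and combining the intervention arms raises it only to 75.5%.

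**The case against.** Several points can be made for the plan.

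- **Nothing is miscalculated.** Each size follows from its own inputs, and the section says a size was derived for each question separately. This stands: the fault is inconsistent assumptions, not an arithmetic slip.
- **The 15 points may be a detectable difference rather than a forecast.** That is a common way to size an added control arm. But the only other rate the plan offers for these arms is 25%, which implies a 7-point benefit that this control arm would usually miss. The plan does not say so.
- **The outcome may differ.** The second calculation states no time window, and the endline interview is at 60 days. However, the Primary outcome section names the 42-day period, and the second calculation holds its other parameters constant, so the same outcome is the likelier reading.
- **The evaluable numbers are inferred.** They rest on adding the three losses. Multiplying them (0.98 × 0.92 × 0.80 = 0.72) gives about 303, 303 and 94, and still no common rate gives 80% for both. With no loss at all, both would reach 80% from a rate of about 30%, but the plan assumes losses.
- **Allocation may be equal.** Blocks of three, six and nine in the Assignment section could imply this, although it would contradict a control arm of 130. With 294 evaluable controls, 18% against 25% has 54% power, and the best smaller power for one arm against control is 77.6%. The shortfall then shrinks but remains.
- **The damage is uneven, and no estimate or type I error is affected.** This stands. At 33% the loss is 80% to 73%; only at 25% is it severe.

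**Conclusion.** The concern holds. The stated 80% power belongs to two different assumed truths about the same arms. Under the plan's own attrition and its 130-woman control arm, non-inferiority power is 73% if the rate is 33%, and power against control is 27% to 31% if the rate is 25%; no rate in between gives 80% for both. The figures assume truly equal intervention arms, summed losses of 30% and a two-sided 0.05 test against control. Non-inferiority power would be higher if text/voice were in fact better than calls, which the plan does not assume. What is at stake is the planned power and the reading of a null result, chiefly for the first two primary objectives.

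**What to change.** In the Sample size section, choose one contraceptive-use rate for the intervention arms, use it in both calculations, and restate the power for each primary question:

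- at 33%: about 73% for non-inferiority and 81% against control;
- at 25%: 80% for non-inferiority and about 27% to 31% against control.

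If both rates are kept as separate planning scenarios, say why and report both powers under each. Add that about 15 points is the smallest difference the 130-woman control arm detects with 80% power, and that a non-significant control comparison does not rule out a 7-point benefit.

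The cost is a few sentences and a less favourable power statement, with no extra participants. Restating does not restore the power. Keeping 80% for non-inferiority at 33% would take 498 per arm instead of 420, which is a separate decision for the sponsor.
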